# Effectiveness of the World Health Organization Safe Childbirth Checklist (WHO-SCC) in preventing poor childbirth outcomes: a study protocol for a matched-pair cluster randomized control trial

**DOI:** 10.1186/s12889-021-11673-0

**Published:** 2021-09-10

**Keywords:** WHO safe childbirth checklist, Quality of care, Burkina Faso, Côte d’Ivoire, Guinea

## Abstract

**Background:**

Women delivering in health facilities in sub-Saharan Africa and their newborns do not always receive proven interventions needed to prevent and/or adequately manage severe complications. The gaps in quality of care are increasingly pointed out as major contributing factor to the high and slow declining perinatal mortality rates. The World Health Organization Safe Childbirth Checklist (WHO-SCC), as a quality improvement strategy, targets low cost and easy to perform interventions and suits well with the context of limited resource settings. In this matched-pair cluster randomized controlled trial, we assess the effectiveness of the WHO-SCC in improving healthcare providers’ adherence to best practices and ultimately improving childbirth outcomes.

**Methods:**

This is a multi-country study. In each country we will carry out a matched-pair cluster randomized controlled trial whereby four pairs of regional hospitals will be randomized on a 1:1 basis to either the intervention or control group. A context specific WHO-SCC will be implemented in the intervention facilities along with trainings of healthcare providers on best childbirth practices and ongoing supportive supervisions. The standard of care will prevail in the control group. The primary outcome is a summary composite metric that combine the following poor childbirth outcomes: stillbirths, maternal deaths, early neonatal deaths, severe postpartum hemorrhage, maternal infections, early neonatal infections, prolonged obstructed labor, severe pre-eclampsia, uterine rupture in the health facility, eclampsia and maternal near miss. The occurrence of these outcomes will be ascertained in a sample of 2530 childbirth events in each country using data extraction. A secondary outcome of interest is the adherence of healthcare providers to evidence best practices. This will be measured through direct observations of a sample of 620 childbirth events in each country.

**Discussion:**

Our study has the potential to provide strong evidence on the effectiveness of the WHO-SCC, a low cost and easy to implement intervention that can be easily scaled up if found effective.

**Trial registration:**

The trial was registered in the Pan-African Clinical Trials Registry on 21st January 2020 under the following number: PACTR202001484669907. https://pactr.samrc.ac.za/TrialDisplay.aspx?TrialID=9662

## Background

The global efforts towards achievement of the 2015 Millennium Development Goals (MDGs) have led to substantial improvement in facility-based child births rates as compared to home deliveries, particularly in sub-Saharan Africa [1, 2], one of the most affected regions by maternal deaths in the world [3]. Yet, maternal and newborns mortality and morbidity rates remain unacceptably high and far above the expected levels [4]. Poor-quality of care in health facilities in low-resource settings is regarded as a major contributing factor to preventable maternal and newborn deaths and disability, justifying why the sustained increase in in-facility births has not been sufficient to reducing maternal and newborns deaths [5]. Quality of care improvement strategies appear to be important and needed as the health facility utilization is raising [6].

Checklist based strategies within the field of surgery have shown effectiveness in improving the adherence of healthcare providers to best practices and ultimately reducing post-surgery mortality and morbidity significantly and have now become a WHO-recommended best practice for all surgical facilities [7, 8]. The WHO Safe Childbirth Checklist (WHO-SCC) is a similar checklist initiative developed as a job aid tool that prompts/reminds healthcare providers on essential best practices at critical points during the course of childbirth care [9]. The checklist is organized around four key pause points during the course of childbirth and is intended to be a bedside tool for healthcare providers to improve the quality and safety of their care by adhering to proven and relatively inexpensive and easy to perform interventions. The rationale behind the checklist strategies in health care is that reminding healthcare providers of essential best practices at critical points can improve their delivery and ultimately help address the human factors of medical errors that arise from basing their implementation on the sole human memory [10]. Best practices are often neglected due to heavy workload or just due to routine or simply failure of human memory. Using a checklist systemizing best practices around the time of childbirth can help overcome these bottlenecks and hence promote quality care during childbirth and the immediate postpartum and neonatal period.

Previous studies have shown that healthcare providers significantly improve their delivery of proven effective and low-cost interventions during the time of childbirth and immediately after childbirth using the WHO-SCC [11–13].

The WHO-SCC is a 29-items checklist which has had inputs from would-be users on the suitability of the content and the implementation strategy at the design phase [9]. The WHO-SCC was then tested in various contexts and has always shown, despite some inconsistencies in the magnitude of the effects [11, 14], effectiveness in improving healthcare providers’ adherence to essential best practices. All these studies emphasized the importance of contextual factors such as leadership commitment, staffing patterns of the health facility etc. and have encouraged context specific adaptation of the checklist (including content change and implementation strategy) in order to reflect local practice and foster ownership. The WHO-SCC targets easy to perform and low costs interventions, yet not always adhered to, as it was shown in a baseline assessment of healthcare providers ‘performance of essential best practices in Burkina Faso and Côte d’Ivoire [15]. Furthermore, the evidence on the effectiveness of the WHO SCC in ultimately improving childbirth outcomes is inconclusive [16] and a recent study suggests that the effects on childbirth outcomes would be more apparent at the referral level of the healthcare system [14]. Our study will seek to assess the effectiveness of a context-specific adapted WHO-SCC in improving healthcare providers’ adherence to EBPs and ultimately in improving childbirth outcomes in referral hospitals of the implementing countries. We postulate that there is an unfavorable cascade leading to poor childbirth outcomes that can be reversed using the WHO-SCC as shown in the study conceptual framework (see Fig. 1). This study was preceded by a first phase where we assessed the gaps in the quality of child birthing care and the acceptability and perceived usefulness of the WHO-SCC in Burkina Faso and Côte d’Ivoire. The results of the first phase showed important quality gaps in delivery care in both countries and the perceived usefulness and the feasibility of the WHO-SCC in both countries conditional on some modifications [15, 17].

**Fig. 1 Fig1:**
[figure not shown]
study conceptual framework. In this figure we depict the cascade leading to poor childbirth outcomes in the framework of the standard of childbirth care and how we postulate the use of the WHO-SCC will unravel this cascade leading to better childbirth outcomes

### Study hypothesis and objectives

We hypothesized that the implementation of a country specific adapted WHO-SCC in referral hospitals, would increase the availability of safe childbirth supplies, the delivery of essential best childbirth practices to the mother-child pair around the time of childbirth, and ultimately leads to improved perinatal health outcomes.

The specific objectives of the study are:
To measure the effectiveness of a modified WHO-SCC in improving healthcare providers’ adherence to EBPs during intrapartum and immediate postpartum care.To assess the effectiveness of modified WHO-SCC in improving the availability of safe childbirth supplies at health facilities levels.To assess the effectiveness of a modified WHO-SCC in preventing poor childbirth outcomes in under-resourced settings.

## Methods

### Trial design

The intervention will be delivered at health facility (cluster) level and outcomes measurements will be carried out at individual participant level. We will use a matched paired cluster randomized controlled trial design, where a pair of health facilities (one intervention and one control) are enrolled in the study at the same time. The study will be conducted in referral hospitals with gynaecologists and where surgical facilities for c-section and blood transfusion services are readily available. Eight (8) regional hospitals (4 intervention and 4 control sites) will be included in the study in each country, giving a total of 24 health facilities (12 in intervention and 12 in control arms) in the three countries. Within each matched pair of health facilities, one will be randomized to receive the intervention and one will receive the standard of care. Facilities will be matched using geographic location within the country, the size of the population covered by the health facility and the annual births volume of the facility. The study will combine two main components: a data extraction component (used to measure the incidence of poor childbirth outcomes) and a direct observation of childbirth practices (to assess the availability of safe childbirth supplies and the adherence of care providers to EBPs).

### Study settings

The study will be conducted in three west-African countries that carry on an important burden of poor childbirth outcomes: Burkina Faso, Guinea and Côte d’Ivoire. The first two are ranked as Low-Income Countries (LIC) per the World Bank ranking, while the latter is ranked as a Low Middle Income Country (LMIC). All these countries have made important progress in shifting deliveries from home to health facilities in recent years. However, these improvements in health facility utilization for childbirths were not followed by the expected improvement in childbirth outcomes. The Maternal Mortality Ratios (MMR) stall and remain unacceptably high and very far from all targets. The latest estimates of MMR were 320, 576 and 617 per 100,000 live births respectively for Burkina Faso, Guinea and Côte d’Ivoire. The neonatal mortality rates are also high for the three countries with respectively 28, 33 and 38 deaths per 1000 in Burkina Faso, Guinea and Côte d’Ivoire [18–20]. The general healthcare delivery system is dominated by the government owned health facilities and is organized in a similar way in each of the three countries, with at the top the national and teaching hospitals that serve as last referral level, at the middle the regional hospitals, and at the bottom the health district system that comprises several primary healthcare facilities organized around a district hospital. The private health sector is embryonic and mainly limited to large cities. The study will be conducted in regional hospitals.

In all three countries, a regional hospital is a last referral hospital for health facilities of various functional classification (primary healthcare facilities, district hospitals) in a particular administrative location called region. It is a level of care where enough capacities are available to adequately manage obstetric complications if they are timely detected as compared to primary healthcare facilities and district hospitals. Because the vast majority of women and their newborns timely detected with complications will not have to be referred to a higher level of care, exposing them to known bad conditions of transportation and related delays, the adoption of the SCC is expected to have more potential to impact morbidity and mortality at this level of care. There are 10 functioning regional hospitals in Burkina Faso, 17 in Côte d’Ivoire and 07 in Guinea. A medical center located in the capital city in Guinea (Conakry) and that has the same level of care as regional hospitals will selected to complement the study sites in Guinea.

### Intervention

The intervention will encompass: (i) the introduction of a modified WHO-SCC in health facilities, (ii) trainings of healthcare providers on good childbirth practices, (iii) and ongoing supportive supervisions. The modified WHO-SCC, as a job aid tool that prompts healthcare providers to remember EBPs that a woman and/or her new-born must receive at four critical junctures during intrapartum and immediate postpartum periods, will be adapted from the WHO-SCC to reflect local contexts and align to the national guidelines of each implementing country. Based on the results of the formative research that showed that the implementation of the WHO-SCC would be more effective if healthcare providers are trained on EBPs complemented by supportive supervisions, the modified WHO-SCC will be introduced in intervention health facilities following a coaching-based approach [12–14, 21]. The formative research also suggested that the content and the ordering of the items of the WHO-SCC should be revised to reflect local practice [17]. This adaptation process will be led by a Technical Advisory Group (TAG) that includes the research teams, the ministries of health and the associations of gynaecologists and paediatricians in each country. The content and wording of the items to be included in the WHO-SCC will be first reviewed and validated by the TAG in a one-day meeting. The resulting WHO-SCC will be pilot tested, and the results will be presented to the TAG in another one-day meeting for the finalization of the WHO-SCC to be implemented in each country. For the introduction of the WHO-SCC in health facilities we will use the coaching based approach with the change model that includes Engage, Launch and Support. Prior to the introduction of the checklist in each health facility, we will engage the administrative and medical leaders to discuss the current deficiencies in the delivery of EBPs to women and new-borns in the intrapartum and postpartum periods and the need for a quality improvement intervention. The results of the formative phase showed important quality-gaps in maternity care. The content of the training sessions will be informed by these quality-gaps and we will put more emphasis on areas needing more improvements. The head medical officer of the maternity ward along with the most experimented midwife in each intervention health facility will have a 2-day orientation training to the modified WHO-SCC and EBPs during childbirth. The trained midwife is meant to be the facility-based coach for day-to-day follow up of the utilization of the checklist after the launch. A one-day orientation session to the WHO-SCC will be organized on site for the staff members of each intervention facility and will be run by the head medical officer, the trained midwife with the support from the research team. After the introduction, the support will be assured by the facility-based coach who will identify barriers to the utilization of the checklist including issues with supplies and help overcome them on a day-to-day basis. New staff members appointed in the facility after the launch will automatically benefit from a 1-day orientation session leads by the head medical officer and the trained facility-based coach. The modified WHO-SCC will be introduced in intervention facilities using a combination of two approaches that were identified as the most effective and acceptable ways for its introduction during the formative research. The first way is to reproduce the modified WHO-SCC in a larger format that will be displayed in the delivery room at the bedside of the woman, allowing healthcare providers to have a glance on it at any time while caring for the mother-new-born pair. Similar approaches are used with the guidelines for the management of post-partum hemorrhage and were found effective by most of the healthcare providers during the formative phase. This approach, while effective in prompting on EBPs at any time, does not however, allow the utilization of the modified WHO-SCC as a documentation tool of EBPs in addition. To allow the utilization of the modified WHO-SCC as a documentation tool as well, we will combine the displaying in delivery room with the attachment of a copy to the partograph.

### Control group

The standard of care will prevail in the control health facilities. There is no childbirth checklist, or a similar tool being used at the moment in health facilities in all the three countries.

### Study participants and recruitment

Pregnant women admitted in the delivery room of participating health facilities for delivery labour during the study recruitment period will be included in the study along with their new-borns. Eligible pregnant women are those for whom a vaginal delivery was considered as first option at admission and the monitoring of the childbirth labour was started. The study will have two components: (i) the direct observation of childbirth practices and (ii) data extraction from patient management tools to assess childbirth outcomes.
Direct observations of child birthing practices

The participants selection into the direct observation component of the study will follow the successive steps below:
ScreeningConsenting eligible participantsPre-inclusion of eligible participantsFinal inclusion of participants after initial examination

Pregnant women presenting in the delivery room will be systematically screened by the data collectors for basic eligibility criteria. Pregnant women that meet the following criteria will not be selected for the consent process:
Admission for a planned C-sectionManifest advanced stage of the laborMinors (age < 18 years)

The data collectors will then consent and pre-include the consenting participants in the study at this stage. After the initial examination will be excluded from the study:
Pregnant women for whom a decision of emergency reference is taken without administration of proper care

Eligible women at this stage are finally included in the study. Pre-inclusion data for women finally excluded will be discarded.
Data extraction to assess childbirth outcomes

The data extraction component of the study will include data from all pregnant women that were admitted in the study period and for whom the labor was monitored in the health facility. We will exclude:
All the women who were admitted in the child birthing room for elective caesarian section (before the labour has begun);All the women and their newborns that were transferred for additional care after a delivery outside of the participating health facility and those received for any other type of obstetric care not related to childbirth (abortions, miscarriages and antenatal care);Pregnant women referred to higher level of care upon admission without proper administration of care at the level of the participating health facility;Mother-newborn pairs for whom provider was prompted to adhere to best practices in order to prevent a life-threatening situation during the direct observation of childbirth practices.

The recruitment will be done by appointed data collectors in each health facility (direct observation) and the facility-based coaches (data extraction). The enrolment into the study for the direct observation of care practices will take place right at the admission in the health facility, before the initial examination is performed. The process of consenting participant will, however, not be caused to delay the health care and for participants that were not able to provide informed consent before initial examination we will not collect data for this pause-point. Data will be collected for the subsequent pause-points if we get informed consent from the women after initial examination. For the data extraction component of the study, the mother-newborn pairs will be consecutively recruited from 2 weeks after the launch of the intervention to 6 months or until the prespecified sample is reached for each health facility. For the direct observation of childbirth care practices, a sample of mother-new-born pairs will also be consecutively recruited among those admitted for childbirth labour in each health facility. This recruitment will start 2 months after the onset of the intervention in intervention facilities and will continue until the calculated sample size for each health facility is achieved.

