#### Secondary outcomes

The first secondary outcome is the level of adherence to EBPs by healthcare providers during childbirth and early postpartum. This will be measured as a rate of successful delivery of key EBPs included in the modified WHO-SCC at each birth event. The provision of key EBPs will be ascertained in a sample of birth events using direct observation with possible cross-validations with data from birth registries and mothers’ health books when necessary. The anticipated best practices to be assessed in this study include: the assessment for need of reference, the use of a partograph, assessment for history and actual bleeding, vision blurred, HIV status, correct use of magnesium sulfate, uterotonics and antibiotics, early initiation of breastfeeding and skin-to-skin contact, and discussions around family planning services.

The second secondary outcome is the rate of availability of essential safe childbirth supplies measured at health facility level. A facility assessment questionnaire will be used to collect data on the availability of essential safe childbirth supplies as baseline assessment prior to the onset of the study. Six months after the launch of the study an end line survey will be conducted using the same questionnaire.

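### Entry to the primary-outcome sample depends on labour monitoring having been started, a staff action taken after randomisation that the intervention may change, so the arms may count different women

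*Protocol article*

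**What the plan says.** Randomisation is by hospital (Trial design): "Within each matched pair of health facilities, one will be randomized to receive the intervention and one will receive the standard of care". Women come later. For the data-extraction component, "the mother-newborn pairs will be consecutively recruited from 2 weeks after the launch of the intervention to 6 months", or until the facility's sample is complete, so the checklist is already in use in one arm.

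Two sentences in Study participants and recruitment set the entry rule. The study-wide one requires that "a vaginal delivery was considered as first option at admission and the monitoring of the childbirth labour was started". The one for data extraction takes in "all pregnant women that were admitted in the study period and for whom the labor was monitored in the health facility". The exclusion list that follows removes, among others, elective caesareans before labour and women who delivered elsewhere.

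Three other statements bear on this:
- Direct observations names admission as the first of the four junctures at which care is observed.
- Secondary outcomes lists "the use of a partograph" among the practices measured as adherence.
- Intervention says the team will "combine the displaying in delivery room with the attachment of a copy to the partograph".

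**The concern.** In a cluster trial whose participants are identified after randomisation, the arms are comparable only if the rule for counting a woman works the same way in both. Here part of the rule is whether staff began monitoring her labour. Staff in intervention hospitals have been trained and have the checklist at the bedside, so they know their arm, and they are being encouraged to work more systematically from admission onward.

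A woman who arrives late and delivers before monitoring starts may be left out of a control hospital's sample, while a similar woman in an intervention hospital may be counted. The opposite pattern is also possible. Such women probably carry a different risk of the composite from the rest, so the two rates could differ with no checklist effect at all.

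Nothing planned would show or repair this. Recruitment is consecutive only among women who meet the condition. Each hospital can stop at its target number, so equal totals could conceal unequal entry. Intention to treat keeps women in the arm to which their hospital was assigned, but it cannot restore women who were never extracted.

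**Working it through.** **The plan's own figure.** Inputs from Sample size: 15% against 7.5%, two-sided 5%, power 80%, ICC 0.01, cluster size 300, non-response 5%.
- Individually randomised size per arm (pooled-variance formula): 278, or 304 with continuity correction.
- Design effect: 1 + (300 − 1) × 0.01 = 3.99.
- 278 × 3.99 = 1109, or 3.70 clusters of 300, rounded up to 4 clusters = 1200. With continuity correction, 304 × 3.99 = 1213.
- 1200 / 0.95 = 1264 per arm, 2528 per country, against 2530 stated.

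The sample size reproduces, and this point does not alter it. The planned effect, 7.5 points, is the yardstick below.

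**Size of the possible bias.** The documents give neither the share of unmonitored labours nor their risk, so the following are assumptions. Let overall risk among labour admissions be 0.15 with no true effect. One arm captures everyone. The other misses a share d of all admissions, whose risk is r. Then

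rate in the arm with losses = (0.15 − d·r) / (1 − d), and false difference = d·(r − 0.15) / (1 − d).

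Suppose 10% or 20% of women are prone to go unmonitored and the control arm misses half of them, so d = 0.05 or 0.10. The last column takes the intervention rate as 0.075.

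| d | r | Control rate | False difference | True risk ratio 0.50 would read |
|---|---|---|---|---|
| 0.05 | 0.30 | 0.135/0.95 = 14.2% | 0.8 points against the checklist | 0.075/0.1421 = 0.53 |
| 0.10 | 0.30 | 0.120/0.90 = 13.3% | 1.7 against | 0.075/0.1333 = 0.56 |
| 0.10 | 0.35 | 0.115/0.90 = 12.8% | 2.2 against | 0.075/0.1278 = 0.59 |
| 0.05 | 0.05 | 0.1475/0.95 = 15.5% | 0.5 in favour | 0.075/0.1553 = 0.48 |
| 0.10 | 0.05 | 0.145/0.90 = 16.1% | 1.1 in favour | 0.075/0.1611 = 0.47 |

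**The reverse pattern.** Suppose the intervention arm is the one that misses high-risk women: 5% to 15% of admissions at risk 30% to 50%, with 10% to 50% of them lost.
- Mildest case, d = 0.05 × 0.10 = 0.005, r = 0.30: 0.005 × 0.15 / 0.995 = 0.1 point in favour of the checklist.
- Most severe case, d = 0.15 × 0.50 = 0.075, r = 0.50: 0.075 × 0.35 / 0.925 = 2.8 points in favour.

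**What the full planned effect would need.** Setting the false difference to 0.075 gives d = 0.075 / (r − 0.15 + 0.075). At r = 0.50, d = 0.075/0.425 = 18% of all admissions lost in one arm only. At r = 0.35, d = 0.075/0.275 = 27%.

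**The case against.** The best defence is that monitoring does not mean a partograph. Neither eligibility sentence mentions one, and partograph use is measured separately as an adherence item. If it were the entry test, that item would be close to 100% by construction. Monitored may mean only that the woman laboured under this hospital's care and was not delivered elsewhere or referred on at once. A working definition could sit in the data collector manual announced under Quality control.

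This stands against a stronger reading: a reader might infer that the checklist directly switches eligibility on, because a copy is attached to the partograph. The documents do not say so, nor that any particular woman is excluded in control hospitals and included in intervention hospitals. Differential entry is a possibility. The defence does not remove the condition, which is stated twice and still turns on what staff did after randomisation. If the intended meaning is only labour under this hospital's care, register-based wording would say so without the risk.

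A reader might also give the vaginal-first condition equal weight, or see a contradiction between it and an exclusion list that names only elective caesarean before labour. Neither goes that far. Mode of delivery is not among the practices listed under Secondary outcomes. The two sentences can be read as inclusion followed by exclusion, and the 15% in Sample size refers to vaginal deliveries. What remains is that the text does not say plainly whether the condition governs data extraction.

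Finally, every input to the size of the bias is assumed, and full capture in one arm against half in the other is a strong contrast. That is accepted.

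**Conclusion.** The point holds for the labour-monitoring condition. Entry to the primary-outcome sample rests on a staff action taken after hospitals were randomised, at a juncture the intervention targets and related to a practice it aims to raise. Selection that differs by arm is therefore possible, and the planned analysis would neither detect nor correct it.

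Direction is unknown. On the assumed inputs the false difference is roughly 0.5 to 2 points. The wider grid, with losses in the intervention arm, spans 0.1 to 2.8. All of this assumes a 15% overall risk among labour admissions and losses confined to one arm. A reader might infer that such selection could by itself manufacture the planned effect. The figures do not support that: it would take the one-sided loss of 18% to 27% of all admissions at risks of 50% to 35%. The realistic harm is a distorted estimate and an uncertain denominator. That justifies changing the wording but does not invalidate the design.

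**What to change.** For the data-extraction component:
- Remove the requirement that labour was monitored. Include every woman whom the admission or birth register records as admitted in labour to, or delivering in, the facility, whether or not monitoring or a partograph was started.
- Keep the exclusions for elective caesarean before labour and for births outside the facility. The exclusions for referral on admission and for prompted births are separate matters that this point does not address.
- Report monitoring as an adherence item.
- Report by arm the number of all labour admissions and the reasons for non-entry.
- Keep vaginal delivery as first option as the target population, and state whether it applies to data extraction, so that the study-wide sentence and the exclusion list read alike. Deleting it would change the research question and the basis of the 15%.
- Add a sensitivity analysis that includes women in labour sent directly to caesarean.

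The cost is small. Birth registries are already a named source. Because data come from records, women left out may be recoverable even if recruitment has begun. A few more sparse charts must be extracted, including those for the sensitivity analysis, and the composite rate may differ from the assumed 15%.
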